#### Assessments of basic characteristic

Assessments of basic characteristics mainly check pulmonary function, dyspnea, and body composition.

The pulmonary function test will be undertaken by specialist personnel. The test will be conducted according to American Thoracic Society / European Respiratory Society (ATS/ERS) standards [25]. Participants will be instructed to breathe, and three reproducible measurements each of FEV1, FVC, and maximal mid-expiratory flow will be obtained (Masterscreen-PFT, Jaeger, Germany). The highest value will be recorded and used for analysis.

The symptoms of dyspnea will be assessed using the mMRC, a five-point scale (0–4) of the severity of dyspnea, with a higher score indicating a higher severity [3].

Body composition will be assessed using DXA (DXA Prodigy, GE Lunar, USA). Patients will be instructed to remove metal objects from their clothing and body and lie on a test platform. DXA support software will calculate body composition including appendicular and body fat mass, appendicular and body skeletal muscle mass, and appendicular and body bone density. In addition, their body mass index will be calculated following measurement of their height and weight using digital scales (4643a, TANITA, Japan).

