## Methods/design

### Design

This is a single-blind, randomized controlled clinical trial, to investigate the effects of prescribed pulmonary exercise in COPD patients by comparing the effects of (1) usual care, (2) prescribed pulmonary exercise, (3) exercising with elastic bands, and (4) prescribed pulmonary exercise combined with exercising with resistance bands in COPD patients. Participants will be enrolled from the respiratory medicine department of Yue-Yang Integrative Medicine Hospital Affiliated to Shanghai University of Traditional Chinese Medicine. The study protocol has been registered with the Chinese Clinical Trial Registry (ChiCTR-1800017405), and the study has been approved by the Ethics Committee of Yue-Yang Integrative Medicine Hospital Affiliated with Shanghai University of Traditional Chinese Medicine (Shanghai, China). All participants will provide written informed consent to participate in the study.

Participants will be randomly assigned to one of four groups according to a random number table generated by computer, with randomization conducted by an independent person not participating in the recruitment process. Random numbers will be placed in sealed opaque envelopes to blind the group allocation. As exercise interventions will be used in the study, concealing the allocation to the therapist and participants will not be possible, so only the outcome assessors will be blinded with a new evaluator replacing the evaluator familiar with the allocation, to maintain blinding. The study procedure is shown in Fig. 2 and the time points of the study in Fig. 3. The protocol follows the SPIRIT 2013 checklist, provided in Additional file 1.

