### Sample size

The sample size was based on detecting a minimum difference of 54 m in the 6MWT [11] between the control group (CG) and the pulmonary exercise group (PG) and used a baseline standard deviation of 57 m [11]. With a power of 80% and an alpha of 5% (two-sided), the minimum sample size per group is 18 to give a total of 72 participants. Assuming a drop-out rate of 20%, the minimum sample size in total is 88 (22 participants in each group). The participants will be recruited to achieve a balanced number of patients with different levels of severity of COPD.

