### Outcome measurement

All participants will undergo assessments within 1 week of being enrolled at baseline and at the end of 3 months. The primary outcomes are the pulmonary function test, 30-s arm curl test, and 6MWT. Secondary outcome measures include the Modified Medical Research Council Dyspnea Scale (mMRC), dual-energy X-ray absorptiometry (DXA), respiratory muscle strength test, peripheral skeletal muscle strength, sEMG, and questionnaires.

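### Taking the highest of three values suits FEV1 and FVC but not maximal mid-expiratory flow, where it favours the least complete blow and overstates the level

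*Protocol article*

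**What the plan says.** Under Outcome measurement, the protocol article states "The primary outcomes are the pulmonary function test, 30-s arm curl test, and 6MWT". It does not say which spirometric variable carries the pulmonary function outcome.

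Under Assessments of basic characteristic, it states that "three reproducible measurements each of FEV1, FVC, and maximal mid-expiratory flow will be obtained", and the next sentence gives the selection rule: "The highest value will be recorded and used for analysis". MMEF is not exempted and is not tied to a particular blow. The same paragraph says "The test will be conducted according to American Thoracic Society / European Respiratory Society (ATS/ERS) standards", but does not reproduce how that standard chooses among blows.

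On blinding, the Design section says "only the outcome assessors will be blinded".

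**The concern.** FEV1 and FVC can only be lowered by a poor or shortened effort, so the highest of three is the natural summary. MMEF behaves differently. The article does not define it; I use the usual meaning, the average flow between 25% and 75% of that blow's own FVC. If the patient stops early, FVC shrinks, the middle half is reached sooner, where flow is faster, and MMEF goes up. The highest MMEF therefore tends to come from the blow with the smallest FVC, and is reported beside an FVC from another blow.

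At stake is the level of one of the three variables recorded for a primary outcome. This is a stated rule that does not fit one of the variables it covers, not a detail left for an analysis plan to supply. Patients with slow emptying are the most exposed, because more of their volume comes late in the blow.

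**Working it through.** **The plan's own figure.** The article gives no figure for MMEF. Its sample size concerns the walking test: "detecting a minimum difference of 54 m in the 6MWT", and it "used a baseline standard deviation of 57 m". The normal approximation gives 2 × [57 × (1.960 + 0.842) / 54]² = 17.5, so 18 per group, as stated. Nothing below alters that number.

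**Inputs.** From the article: three measurements, the highest used, and the measurements described as reproducible with no tolerance given. Emptying curves, stop times and FVC tolerances are my assumptions.

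**Step 1: direction, single-exponential emptying.** If exhalation stops at a fraction c of full FVC, MMEF is proportional to 0.5c / ln[(1 − 0.25c) / (1 − 0.75c)].

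| c | Value | Change from full exhalation |
|---|---|---|
| 1.00 | 0.4551 | – |
| 0.98 | 0.4680 | +2.8% |
| 0.95 | 0.4870 | +7.0% |
| 0.90 | 0.5178 | +13.8% |

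**Step 2: a slowly emptying lung.** Assume V(t) = 1.0(1 − e^(−t/0.6)) + 1.7(1 − e^(−t/4)) litres, so FEV1 is 1.19 L. MMEF = 0.5 × FVC / (t75 − t25), with FVC taken at the stop time.

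| Stop time | FVC (L) | t25 (s) | t75 (s) | MMEF (L/s) | Change |
|---|---|---|---|---|---|
| 12 s | 2.62 | 0.404 | 3.355 | 0.443 | – |
| 8 s | 2.47 | 0.375 | 2.827 | 0.504 | +14% |
| 6 s | 2.32 | 0.347 | 2.369 | 0.574 | +30% (29.5%) |

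**Step 3: effect of the rule.** Simulate three blows with stop times uniform over a range, and divide the highest MMEF by the MMEF of the largest-FVC blow. With no limit on FVC agreement, the ratios are 1.07 (8–12 s), 1.11 (6–10 s) and 1.13 (6–12 s). The article asks for reproducible measurements, so I also kept only triplets whose FVCs agree within an assumed tolerance:

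| FVC agreement | Overstatement |
|---|---|
| within 0.05 L | about 3% |
| within 0.10 L | 5% to 6% |
| within 0.15 L | 7% to 8% |

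In the single-exponential model, with shortfalls uniform up to 2%, 5% or 10% of FVC, the highest-of-three rule overstates full-exhalation MMEF by 2.1%, 5.3% or 10.4%. The largest-FVC blow overstates it by 0.7%, 1.8% or 3.5%. The gaps between the rules are 1.4, 3.5 and 6.9 percentage points. For scale, 2% and 5% of 2.62 L are 0.05 and 0.13 L.

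These runs have no other noise, so the highest MMEF always comes from the shortest blow. With 3% random noise added to the single-exponential model, it does so 43%, 56% and 70% of the time, against 33% by chance.

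**Step 4: what a difference between arms would need.** Give both arms identical lungs (the Step 2 model) and change only exhalation time in a trained arm:

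| Assumed change in blow length | Artefact, highest MMEF | Artefact, largest-FVC blow |
|---|---|---|
| every blow 2 s longer (6–10 s to 8–12 s) | −9.9% | −6.2% |
| every blow 1 s longer (6–10 s to 7–11 s) | −5.7% | −3.5% |
| only short blows disappear (6–12 s to 8–12 s) | −7.6% | −1.6% |

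With no such change the artefact is zero under either rule.

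**The case against.** The strongest reply is that the rule is identical in all four arms and at both visits, and assessors are blinded, so a shared upward shift need not bias the group-by-time comparison. That stands. A reader might infer that the breathing exercises, with their *hu* and *si* sounds, lengthen exhalation in the exercised arms and so bias the comparison. The article does not support this. It names the sounds and describes posture and breathing training, but nowhere says the programme prolongs a maximal forced exhalation in the laboratory.

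Second, reproducible blows limit how far FVC can differ. This also stands, and is why the unrestricted 14% and 30% figures should not be taken as the likely effect. It does not remove the bias: about 3% remains in the two-compartment model even with agreement within 0.05 L.

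Third, changing the rule removes only part of any arm-related artefact. When every blow lengthens by 2 s, 6.2 of the 9.9 points remain, because MMEF depends on expired volume whichever blow is read.

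Fourth, MMEF is peripheral: it is mentioned once, the pulmonary function effects cited from earlier work are on FEV1 and its ratios, and the sample size rests on the walking test. This limits the importance of the point, but MMEF is still recorded within a primary outcome that names no leading variable.

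Last, the sentence may be shorthand for the cited ATS/ERS rule. That cannot be checked here, and nothing above relies on what the standard says. As written, the article applies the highest value to all three variables.

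**Conclusion.** The concern holds as a modest measurement point. Applied to MMEF, the highest-of-three rule favours the least complete blow and overstates the level. The direction follows from the definition of MMEF. The size does not come from the article: about 3% to 8% in the assumed two-compartment lung with FVCs agreeing within 0.05 to 0.15 L, and less in a single-exponential lung (1.4 to 3.5 points for shortfalls up to 2% to 5%).

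A biased treatment comparison is possible only if completeness of exhalation changes differently by arm, and the documents do not show that. FEV1, FVC and the sample size are unaffected. This is a cheap improvement, not a threat to the trial's main conclusions.

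**What to change.** Replace the single selection sentence with two rules. Keep the highest FEV1 and the highest FVC. Take MMEF from one acceptable blow chosen on its volumes, for example the largest FEV1 + FVC or the largest FVC, and use the same criterion at both visits. The calculations above tested only the largest-FVC version. Trial status says recruitment is under way, so re-extract MMEF for patients already tested wherever their curves are stored.

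The cost is one sentence and a different read-out of blows already recorded, with no extra testing. Reported MMEF will be slightly lower. Because the change reduces but does not remove the dependence on expiratory time, MMEF should be interpreted alongside FVC.

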#### Muscle function tests

Assessments of muscle function mainly check respiratory muscle strength, and dominant upper and lower limb isokinetic muscle strength and sEMG.

Respiratory muscle strength, expressed as maximal inspiratory pressure and maximal expiratory pressure, will be assessed by specialist personnel following the ATS/ERS guidelines [26] using spirometry (Masterscreen-PFT, Jaeger, Germany). The maximal inspiratory pressure will be obtained when the subject exhales to the level of their residual functional volume, while the maximal expiratory pressure will be obtained when the subject inhales to the level of their total lung volume. Stable pressure readings will be recorded. The two measurements will be taken at least three times, and the highest result will be used for analysis. The interval between two consecutive measurements will be at least 1 min.

Peripheral skeletal muscle strength will be assessed using a biomechanical test and training system (CON-TREX, Physiomed, Germany). According to the user manual, subjects will be instructed to sit straight in a special chair, and the dominant limb muscle strength, including that of elbow and knee joints, will be evaluated. Straps will be applied across the chest and pelvis of the subject to prevent extraneous body movements during muscle contractions.

For the elbow joints, the alignment between the dynamometer rotational axis and the elbow joint’s rotational axis (humeral lateral condyle) will be checked before testing. The movement axis is parallel to the forearm and a strap will be used to maintain the connection. At the end of the movement, a hand will be placed to provide support in generating strength. After the subject is placed in a standard position, they will be instructed to perform flexions and extensions two or three times to determine the range of motion and for them to become familiar with the test.

For the knee joints, the alignment between the dynamometer rotational axis and the knee joint’s rotational axis (knee joint fibula capitulum) will be checked before the test. A resistance pad will be placed 2–3 cm above the ankle and a strap used to stabilize the dominant side. An obstacle will be used to prevent contraction of the disadvantaged limb. After the subject is placed in a standard position, they will be instructed to perform flexions and extensions two or three times to determine the range of motion and for them to become familiar with the test.

The test regimen for both elbow and knee joints consists of isokinetic concentric contractions. First, the subject will be asked to perform five continuous contractions at 60°/s of maximal flexion and extension, from which the computer will automatically calculate the maximum of five repetitions as the peak torque (N m) and the relative peak torque obtained by dividing the peak torque by the body weight (N m/kg). Then, the subject will be asked to perform 30 continuous contractions at 180°/s of maximal flexion and extension, from which the computer will automatically calculate the total work (joules) for the 30 repetitions. Verbal encouragement will be provided during testing to encourage maximum effort.

The peripheral skeletal muscles will be assessed by a wireless remote-sensing sEMG test and analysis system (Trigno™ Lab, Delsys, USA). The major muscles tested include the biceps and triceps in the dominant arm, and the rectus femoris, vastus medialis, and vastus lateralis in the dominant leg. The sEMG signal sampling rate will be set to 2000 Hz. In accordance with Surface Electromyography for the Non-Invasive Assessment of Muscles (SENIAM) (Simsek D, Different fatigue-resistant leg muscles and EMG response during whole-body vibration. Journal of Electromyography and Kinesiology. 2017, 37: 147-154) recommendations, the measurement sites will be prepared by shaving followed by cleaning the skin with alcohol. Surface electrodes will be placed at the highest point of the muscle belly during a contraction and parallel to the longitudinal arrangement of the muscle fibers. For the biceps and triceps, the sensor will be placed at the highest point of the muscle belly during flexion and extension. For the rectus femoris, the sensor will be placed midway between the anterior superior spine and the upper patella. For the vastus medialis, the sensor will be placed at 4/5 of the distance from the anterior superior spine to the medial joint of the knee. For the vastus lateralis, the sensor will be placed at the 2/3 of the distance from the anterior superior spine to the upper patella [27]. After positioning the electrodes, the experimental session will start with maximum voluntary isometric contractions measured by a MicroFET3 (Hoggan Scientific LLC, USA). The subjects will perform one trial to become familiar with the test and then perform two repetitions, each 5 s in duration. Verbal encouragement will be provided during the test to encourage maximum effort. There will be a 2-min rest between contractions.

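### The vastus lateralis sEMG site is defined on the rectus femoris line with no lateral landmark, which conflicts with the section's own muscle-belly rule

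*Protocol article*

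**What the plan says.** Surface electromyography is one of the secondary outcomes listed under Outcome measurement: "respiratory muscle strength test, peripheral skeletal muscle strength, sEMG, and questionnaires". The Muscle function tests section names five muscles on the dominant side. Two are in the arm (biceps and triceps) and three in the thigh: "the rectus femoris, vastus medialis, and vastus lateralis in the dominant leg".

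The section opens its placement instructions with a general rule: "Surface electrodes will be placed at the highest point of the muscle belly during a contraction". It then gives a site for each muscle. The arm muscles are located by repeating the belly rule. The thigh muscles are located by fractions of a line between two landmarks:

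- Rectus femoris: "For the rectus femoris, the sensor will be placed midway between the anterior superior spine and the upper patella".
- Vastus medialis: "the sensor will be placed at 4/5 of the distance from the anterior superior spine to the medial joint of the knee".
- Vastus lateralis: "For the vastus lateralis, the sensor will be placed at the 2/3 of the distance from the anterior superior spine to the upper patella".

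The article attributes these sites to a cited placement source (reference 27), which is not at hand.

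**The concern.** The rectus femoris and vastus lateralis sites are fractions of a line with the same two end points. The vastus medialis has a line of its own ending on the medial side of the knee, but the vastus lateralis has no lateral counterpart. The protocol uses the shared line to find the muscle at the front of the thigh. Moving further down it does not bring the sensor to the muscle on the outer side.

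An assessor who uses the written coordinates and one who uses the general belly rule could therefore place the vastus lateralis sensor in different spots. Two things are at stake. If the coordinates are followed, the recording may be reported under the wrong muscle's name. If different assessors follow different rules, the site may move between baseline and 3 months and add error to the within-patient change. The second is possible because the Design section provides for replacing an evaluator who has become aware of the allocation.

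**Working it through.** The documents give no figure to reproduce here. The check sets the landmark rules side by side.

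**Inputs, all from the Muscle function tests section**

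| Muscle | Line starts at | Line ends at | Fraction | Side-specific end point? |
|---|---|---|---|---|
| Rectus femoris | anterior superior spine | upper patella | 1/2 | no |
| Vastus lateralis | anterior superior spine | upper patella | 2/3 | no |
| Vastus medialis | anterior superior spine | medial joint of the knee | 4/5 | yes, medial |

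**Step 1: collinearity.** Two points defined as fractions of one line both lie on that line. The rectus femoris site is at 0.500 of its length and the vastus lateralis site at 0.667. Their sideways offset from the line is zero. This follows from the text alone.

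**Step 2: spacing along the line.** 2/3 − 1/2 = 1/6 of the line length. The documents give no thigh length. For an assumed line of 40, 45 or 50 cm:

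- 40/6 = 6.7 cm
- 45/6 = 7.5 cm
- 50/6 = 8.3 cm

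These figures describe only how far apart the sensors are. They do not show what the lower one would record.

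**Step 3: comparison with the general rule.** The belly rule sends the sensor to the most prominent part of the named muscle. For the vastus lateralis that is on the outer thigh, off the front-of-thigh line. This step rests on basic anatomy, not on a figure in the documents. The belly rule and the written coordinates therefore cannot both be met for this muscle.

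**Step 4: extent.** The conflict affects 1 of 3 thigh channels and 1 of 5 muscles. sEMG is itself one of the six secondary outcome measures listed under Outcome measurement.

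**The case against.** The strongest reply is that the belly rule comes first and governs. An assessor who reads the whole section, and is told that the target is the vastus lateralis, would find that muscle as it contracts and use the 2/3 fraction only for the level along the thigh. This may well happen in practice, and it stands to this extent: the text does not show that the wrong muscle will be recorded. It does not remove the conflict, because the text never says which rule prevails. For the thigh muscles it gives coordinates where for the arm muscles it repeats the belly rule, so following the coordinates literally is also a fair reading.

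A reader might infer more: that the sensor is bound to record the front of the thigh, that the channel duplicates the rectus femoris, and that vastus lateralis data already collected are invalid. The documents support none of these. They do not say what a sensor at the 2/3 point would pick up, and a site several centimetres further down, perhaps over tendon, need not repeat the signal from the muscle belly. Nor do they say where assessors have actually placed the sensor.

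It can also be said that the cited source may give a correct site and that the article merely dropped a word such as lateral. That is the likely cause. The printed coordinate would still need correcting, since this is not a detail left to a manual: the article states the site explicitly.

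Finally, the outcome is secondary, limb strength is measured separately by isokinetic dynamometry, and the same placement text applies to all four arms with blinded assessors. All of this stands and sets the weight of the point.

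**Conclusion.** The point holds as a minor correction. The article puts the vastus lateralis site on the rectus femoris line without a lateral landmark, and this conflicts with its own rule to place electrodes over the muscle belly. The collinearity is certain from the text. That the written site misses the vastus lateralis rests on basic anatomy, and the spacing of 6.7 to 8.3 cm rests on an assumed line of 40 to 50 cm.

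The possible consequences are a mislabelled channel, or a site that shifts between visits, depending on which rule is followed and by whom. Neither is shown to have occurred. The effect is confined to one of five muscles in a secondary outcome. It does not touch the primary outcomes or the sample size, and because the same text applies to every arm it does not favour any of them.

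**What to change.** 1. Give the vastus lateralis line a lateral end point, for example the lateral side of the patella. This wording is only an example; check the landmark and the fraction against the cited placement source before adopting them.
2. State how the thigh coordinates and the muscle-belly rule work together, so that an assessor knows which prevails if they disagree.
3. Require the same site at baseline and 3 months for each patient, including when an evaluator is replaced.
4. For patients already tested, first establish where the sensor was placed. Set vastus lateralis data aside only if it was placed on the written line; otherwise keep them.

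The cost is about one sentence in the assessment instructions, a short re-briefing of assessors, and a check of past placements. The article's Trial status section describes the study as still recruiting, so the change could apply to later assessments. It alters neither the design nor the sample size.
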